### Data collection

Once ethics approval is received at the participating sites, collection of pre-implementation data will begin. Data will be collected three times per day (in the morning, at lunch, and in the afternoon) and two days each week (excluding holidays and weekends). This data collection will occur over three phases: pre-implementation (10 weeks or 20 assessment days), implementation (8 weeks or 16 assessment days), and post-implementation (20 weeks or 40 assessment days) (Table 2). In order to detect a 10% decrease for the patients being in bed after the intervention, based on a power of 0.8 and type I error of 0.05, correlation for AR(1) of 0.4 and proportion of patients being in bed before the intervention at 66%, the required number of data collection points is 40.

Baseline data will be collected on eligible patients including age, gender, place of residence prior to admission, admitting diagnosis, and functional status prior to admission from the chart. This information will be collected retrospectively from chart review.

### Analysis

#### Quantitative analysis

The interrupted time series design will be used as it is more robust than a simple before-after study design. The primary outcome is the proportion of patients aged 65 and older who are mobilized three or more times daily during the audit. Mobilization is defined as not being in bed. The primary analysis will compare the proportion of inpatients aged 65 years and older who were mobilized in the pre-, during and post-intervention periods. We will also perform subgroup analyses across the different participating hospitals to provide site-specific data. The unit of experimentation will be based on multiple temporal assessments. For the primary outcome, 20 consecutive time points over 10 weeks will be used to create a pre-intervention model. To evaluate whether this pre-intervention model adequately describes the baseline, time series models will also be estimated for the entire 76 time points (pre- and post-intervention). We anticipate that each site will obtain data on 35 to 45 patients per audit. Segmented linear regression models will be performed to examine the impact of the intervention on the primary outcomes [34]. The initial time series regression model included terms estimating changes in the level and trend of outcome rates after intervention, in addition to the constant term, and the term estimating changes in baseline trend over time. Durbin’s alternative test [35] will be used to examine for the presence of serial autocorrelation among the observations, and models will be corrected for autocorrelation as required using the Cochrane-Orcutt methodology [36]. All statistical analyses will be conducted using SAS version 10.0, and statistical significance will be set at p <0.05.

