**Methods/design:**

Implementation of our early mobilization strategy is guided by the Knowledge to Action Cycle. Through focus groups with frontline staff, we will identify barriers and facilitators to early mobilization. We will tailor the intervention at each site to the identified barriers and facilitators, focusing on the following key messages: to complete a mobility assessment and care plan within 24 hours of the decision to admit patients aged 65 years and older; to achieve mobilization at least 3 times per day; and, to ensure that mobilization is scaled and progressive. The primary outcome, number of patients observed out of bed, will be documented three times per day (in the morning, at lunch and in the afternoon), two days each week. This data collection will occur over 3 phases: pre-implementation (10 weeks), implementation (8 weeks), and post-implementation (20 weeks).

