### Outcomes

Using an integrated KT approach, the outcomes were selected and prioritized by the team members (including healthcare providers, educators, patient advocates, and decision-makers) to ensure that they are patient-centred and relevant to the institutions. The outcomes that were selected will also be of interest to others interested in implementing this initiative in other provinces and jurisdictions.

The primary outcome is the percentage of ‘out of bed’ observations amongst older patients measured by an audit of directly observed activity at three points during the day. A negative default of lying in bed will be used if the information is not clear from direct observation (for example, if the patient is off the ward for a test). Through the intervention, we seek to decrease the number of patients observed to be in bed during the assessment periods. Precision and accuracy of this strategy for detecting mobilization events have been evaluated against observations conducted every 15 minutes (inter-rater agreement, kappa 0.83; positive likelihood ratio 12.2; negative likelihood ratio 0.06). Currently, our participating sites do not routinely collect data on mobilization of patients. Secondary outcomes include: acute length of stay, functional status at admission and at discharge (Activities of Daily Living [ADL]/ Instrumental Activities of Daily Living [IADL]), discharge destination, falls, injurious falls; and perceptions of patients, informal caregivers, family members, and healthcare providers (Table 2).

**Table 2 T2:** Study outcomes and source of data

	**Outcome**	**Definition**	**Data source**
**Primary**	Frequency of mobilization of patient	% of patients documented ‘not in bed’ during audit	Direct observation
**Secondary**	Length of stay	Days	Chart abstraction or hospital decision support unit (HDSRU)
	Functional status at admission and at discharge (ADL/IADL)	% patients in each category of ADL status	Chart abstraction
	Discharge destination	% patients discharged to location other than LTC	Chart abstraction or HDSRU
	Falls	Number of incident reports filed	Chart abstraction or HDSRU
	Injurious falls (fractures, subdural hematoma)	Number reported	Chart abstraction or HDSRU
	Perceptions and satisfaction of patients, informal caregivers, family members and healthcare	Qualitative data	Interviews
	Rate of documentation	Change in documentation of baseline and discharge functional status	Document review

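### The primary outcome is defined in two different ways: as the percentage of out-of-bed observations and as the proportion of patients mobilized at least three times a day. The power inputs do not fit the second.

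*Protocol article*

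**What the plan says.** The article describes the primary outcome in several places.

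- **Abstract, Methods/design:** "The primary outcome, number of patients observed out of bed, will be documented three times per day".
- **Outcomes, text:** "The primary outcome is the percentage of ‘out of bed’ observations amongst older patients measured by an audit of directly observed activity", at three points in the day. A look that is unclear, for example because the patient is off the ward for a test, counts as in bed.
- **Outcomes, Table 2:** the percentage "of patients documented ‘not in bed’ during audit", with no rule for combining a day's looks.
- **Quantitative analysis:** "The primary outcome is the proportion of patients aged 65 and older who are mobilized three or more times daily during the audit". The same paragraph adds "Mobilization is defined as not being in bed" and then words the comparison without any threshold: "The primary analysis will compare the proportion of inpatients aged 65 years and older who were mobilized in the pre-, during and post-intervention periods".

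Data collection sets three looks per audit day (morning, lunch, afternoon). Its power statement uses a 10% decrease in patients in bed, power 0.8, type I error 0.05, AR(1) correlation 0.4 and "proportion of patients being in bed before the intervention at 66"%, and arrives at 40 data collection points.

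**The concern.** Two sentences each state what the primary outcome is, and they name different quantities. In Outcomes the unit is the observation. In Quantitative analysis the unit is the patient on an audit day, and a threshold is applied. With three looks a day, three or more can only mean all three. A patient out of bed at two of three looks contributes 2/3 to the first measure and 0 to the second. The in-bed default widens the gap, because a single off-ward look fails the patient's whole day under the second version.

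Two analysts working from different sections would report different baselines, effects and p-values from the same audit data. Study status says that baseline collection is complete at all sites, and the Discussion says that the data collector is not blinded to phase. A definition chosen after the post-implementation results are known would be hard to defend.

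**Working it through.** **The plan's own figure.** The 40 points cannot be strictly reproduced, because the article gives no formula, no standard deviation for the series and no split between phases. A rough check treats the problem as two proportions, 66% versus 56% in bed, two-sided:

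- Observations per phase: 373.
- AR(1) inflation: (1 + 0.4)/(1 − 0.4) = 2.333.
- Patients per audit per site (Quantitative analysis): 35 to 45.
- Total points over two equal phases = 2 × 373/m × 2.333. This gives 49.7 at m = 35, 43.5 at m = 40 and 38.7 at m = 45.

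At m = 45, 19.3 points per phase round up to 20 + 20 = 40. The stated figure is therefore plausible for a 66% in-bed proportion with an absolute 10-point drop, but only under assumptions that the article does not state. A relative 10% decrease gives 87 to 112 points.

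**What the per-look rate implies for the three-times criterion.** Out of bed per look is 1 − 0.66 = 0.34 before, and 0.44 after if the 10% is absolute. The article gives no within-patient correlation ρ between looks, so it is varied here from 0 (independent) to 1 (always agree). Under a beta-binomial model,

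P(all three) = p × [p(1 − ρ) + ρ] × [p(1 − ρ) + 2ρ]/(1 + ρ).

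At ρ = 0 this is p³: 0.34³ = 0.039 and 0.44³ = 0.085. At ρ = 0.4 and p = 0.34 it is 0.34 × 0.604 × 1.004/1.4 = 0.147.

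| ρ (assumed) | Before | After | Gain (points) |
|---|---|---|---|
| 0 | 3.9% | 8.5% | 4.6 |
| 0.2 | 9.0% | 15.2% | 6.2 |
| 0.4 | 14.7% | 22.2% | 7.5 |
| 0.6 | 20.9% | 29.4% | 8.5 |
| 1 | 34% | 44% | 10 |

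If the 10% is relative, the in-bed share falls to 0.66 × 0.9 = 59.4%, so 40.6% are out of bed. The all-three gain then runs from 0.406³ − 0.34³ = 0.067 − 0.039, about 2.8 points, to 6.6 points.

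**Effect on the number of time points.** The same approximation with m = 40, applied to the all-three rates:

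- ρ = 0: 435 per phase, so 2 × 435/40 × 2.333 = 50.8 points.
- ρ = 0.3 (11.8% to 18.7%): 426 per phase, 49.7 points.
- ρ = 0.5 (17.8% to 25.8%): 417 per phase, 48.7 points.
- ρ = 1: 373 per phase, 43.5 points, the same as the per-look measure.

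This is crude. It credits each patient with one result per time point, although three looks carry more information about a per-look percentage unless they always agree. It uses one site's patient count, and it omits the trend terms of the planned segmented regression.

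**The case against.** The strongest reply is that one stray sentence is at fault. The abstract, the Outcomes text and Table 2 can all be read as the same per-look measure, loosely worded. The Quantitative analysis section itself defines mobilization as not being in bed and states the comparison with no threshold. The three-times wording may have been carried over from the intervention's key message of mobilization at least three times per day. This is a fair account of how the conflict may have arisen. It does not remove the conflict: the sentence stands in the analysis section as the definition of the primary outcome.

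Several stronger readings are tempting, but the article does not support them.

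- *There are four incompatible definitions.* Only the Outcomes text and the Quantitative analysis section clearly conflict.
- *The power statement fits only the percentage of observations.* It speaks of patients in bed, so it fits Table 2 read per look equally well. It fails to fit only the three-times criterion.
- *The trial is underpowered for the three-times outcome.* The rough calculation moves from about 44 to at most 51 points at 40 patients per point. The planned 20 pre and 40 post points are worth 2 × 2/(1/20 + 1/40) = 53 equally split ones. At 35 patients and independent looks the need would be 2 × 435/35 × 2.333 = 58, so adequacy is not shown either.
- *The validation figures belong to the per-observation measure.* Outcomes does not say whether the likelihood ratios are per look or per patient-day.
- *Three snapshots cannot count mobilizations.* The Discussion already acknowledges that the audit is only an estimate, and activity between looks is missed under either definition.
- *The outcome has been switched.* Nothing shows this. The risk arises only if the choice is made after results are seen.

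**Conclusion.** The point holds as an internal contradiction in the definition of the primary endpoint, and it must be resolved. It rests on the text alone: two explicit definitions, three looks per day and no section that reconciles them. An unseen analysis plan does not excuse a conflict printed in the article.

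The size is in the endpoint itself. Under the three-times version the baseline could be anywhere from 3.9% to 34%, and a 10-point per-look gain anywhere from 4.6 to 10 points. These ranges assume that the 66% applies to each look, that the 10% is absolute, and that the within-patient correlation lies between 0 and 1. The two definitions coincide only if each patient's three looks always agree. The effect on required time points appears moderate on a rough approximation, and the stated 40 is neither confirmed nor refuted.

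**What to change.** Make the percentage of out-of-bed observations per audit day the single primary outcome, worded identically in the abstract, Outcomes (text and Table 2) and Quantitative analysis. The denominator should be all scheduled observations of eligible patients, with unclear or off-ward looks counted as in bed, as Outcomes already states. Dropping such looks as invalid would change the outcome. Delete the three-or-more-times-daily condition from the primary definition, and name out of bed at all three looks as a secondary outcome.

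Record the date of the decision relative to the completed baseline collection, and make it before post-implementation data are analysed. If the three-times outcome is kept as primary instead, restate the power inputs in Data collection (baseline rate and target change) on that scale.

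The cost is a wording change and a dated record. Both outcomes come from the same audits, provided that looks are recorded per patient. Keeping the three-times outcome as primary would also need a new power calculation.

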### Study design

The impact of the knowledge translation (KT) intervention will be evaluated using an interrupted time series design. In the 10-week pre-implementation period, we will engage local users and contextualize the implementation strategy. This period will be followed by an 8-week implementation roll-out period and then by a 20-week post-implementation period (Table 1).

**Table 1 T1:** Duration of study phases and data collection

**Study phase**	**Pre intervention**	**Intervention**	**Post intervention**
Duration	Twice a week for 10 weeks	Twice a week for 8 weeks	Twice a week for 20 weeks
Primary Outcome Data points	20 audits	16 audits	40 audits
Secondary Outcomes	Chart abstractions of HDSRU	Chart abstractions of HDSRU	Chart abstractions of HDSRU

We are using an integrated KT approach, which refers to a collaborative process whereby researchers and research users work together to design the implementation process. This project was developed by knowledge users, specifically front line clinicians, patient advocates, and healthcare managers.

Our KT approach is informed by the Knowledge to Action (KTA) Cycle developed by Graham and colleagues [18]. It highlights processes relating to knowledge creation, distillation and use. In this model, the knowledge creation funnel represents knowledge generation, synthesis, and development of knowledge tools. The action parts of the cycle are based on a systematic review of planned action theories and include the processes needed to implement knowledge in healthcare settings, specifically, problem identification; assessment of determinants of KT; selecting, tailoring, implementing and evaluating KT interventions; and determining strategies for ensuring sustained knowledge use.

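### The segmented regression has one interruption but is fitted to all 76 audits, so the 16 roll-out audits have no terms of their own and a gradual effect would be mis-estimated

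*Protocol article*

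**What the plan says.** All references are to the protocol article.

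- **Phases.** Study design describes a 10-week pre-implementation period and continues: "This period will be followed by an 8-week implementation roll-out period and then by a 20-week post-implementation period". Data collection counts the audits: "pre-implementation (10 weeks or 20 assessment days"), "implementation (8 weeks or 16 assessment days") and "post-implementation (20 weeks or 40 assessment days").
- **Baseline model.** Quantitative analysis: "20 consecutive time points over 10 weeks will be used to create a pre-intervention model".
- **Full-series model.** The next sentence, on whether that baseline model is adequate, says "time series models will also be estimated for the entire 76 time points (pre- and post-intervention").
- **Regression terms.** "The initial time series regression model included terms estimating changes in the level and trend of outcome rates after intervention", besides a constant and a baseline trend. That makes four parameters and one interruption.
- **Primary comparison.** "The primary analysis will compare the proportion of inpatients aged 65 years and older who were mobilized in the pre-, during and post-intervention periods".

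The article does not say at which audit the interruption sits or how the roll-out audits are coded.

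**The concern.** The stated terms, the stated number of points and the stated primary comparison do not fit together. The primary comparison has three periods, but the regression can separate only two. The 76 points carry a two-phase label, yet that number is reached only by counting the roll-out.

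A four-term model fitted to all 76 points must put the 16 roll-out audits on one side of its single break. The pre-intervention model is built on 20 points, so the natural reading is a break after audit 20, with the roll-out counted as post. The model then assumes that the whole level change is present from audit 21. An education programme delivered over eight weeks may well act gradually. In that case the roll-out audits pull the fitted level down and tilt the fitted post trend upward. This affects the analysis on which the main conclusion rests.

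**Working it through.** **Count.** 20 + 16 + 40 = 76, the article's figure. Pre plus post alone is 20 + 40 = 60. The difference is the 16 roll-out audits.

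**Inputs.** From Data collection: 66% in bed before the intervention (34% out of bed), a 10% decrease as the target and AR(1) correlation 0.4. Assumed, because the article does not give them: the 10% is 10 percentage points, the baseline is flat, the rise is linear across audits 21-36, and the gain is then sustained. The calculation is noise-free.

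**Stated model, break after audit 20, ordinary least squares.** With its own level and slope after the break, the post segment is a straight line through audits 21-76. Let s = audit − 20, so s = 1 to 56. The gain is 10s/16 for s ≤ 16 and 10 thereafter.

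- Sum of gains: (10/16) × 136 + 40 × 10 = 85 + 400 = 485. Mean: 485/56 = 8.661. Mean of s: 28.5.
- Sum of s × gain: (10/16) × 1,496 + 10 × (1,596 − 136) = 935 + 14,600 = 15,535.
- Sxy = 15,535 − 28.5 × 485 = 1,712.5. Sxx = 56 × (56² − 1)/12 = 14,630.
- Trend change = 1,712.5/14,630 = +0.117 points per audit. The true post-implementation trend is zero.
- Level change = 8.661 − 28.5 × 0.117 = 5.3 if time since the break starts at 1, or 5.4 if it starts at 0.
- Modelled effect at audit 37 (s = 17): 5.325 + 17 × 0.117 = 7.3. At mid-post (s = 36.5) it is 9.6, and at audit 76 (s = 56) it is 11.9. The true value is 10 throughout.

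**Same model, generalised least squares with AR(1) = 0.4.** This matters because the plan corrects for autocorrelation where it is found. The level change is 4.3 to 4.4. The modelled effect is 5.5 at audit 37 and 6.8 at mid-post.

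**Dependence on the shape of the effect (break after audit 20, least squares, time since the break from 0).**

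| Assumed shape of a 10-point gain | Level change |
|---|---|
| Immediate step at audit 21 | 10.0 |
| Linear over roll-out | 5.4 |
| Step midway through roll-out | 5.0 |
| Step at the end of roll-out | 1.1 |

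In the last three rows a spurious trend change of +0.12 to +0.22 points per audit appears. If the 10% is relative (6.6 points), the linear case gives a level change of 3.6.

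**With the roll-out separated.** A three-segment model (breaks after audits 20 and 36), or one that omits audits 21-36 and reads the level at audit 37, returns 10.0 at audits 37 and 76 for all four shapes by least squares.

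**Precision at audit 37.** Assume 14 hospitals × 40 patients (the middle of the anticipated 35 to 45) = 560 per audit, binomial noise and AR(1) = 0.4. The SD per audit is √(0.66 × 0.34/560) = 2.0 points. The standard error of the effect at audit 37 is 2.85 points for the single-break model and about 3.0 to 3.1 when the roll-out is modelled separately or excluded.

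**The case against.** The strongest reply is that the article is inconsistent rather than committed to a wrong model. It keeps the roll-out as its own phase in Study design, in Table 1 and in the primary comparison. It calls the regression initial, it fixes no break, and an analysis plan that is not shown may code the roll-out audits properly. That stands as far as the final analysis is concerned. It does not remove the point: the terms, the 76 points and the two-phase label are stated, and together they leave the roll-out no place of its own.

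A second reply is that the level coefficient is not the whole estimate. It describes audit 21, where a linear rise has barely begun, and the trend term later makes up ground. This also stands. By least squares the mid-post effect is 9.6, close to 10, so the fairer comparison is at audit 37: 7.3, or 5.5 with AR(1) weighting.

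A reader might infer four stronger things that the article does not support:

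- **The roll-out contaminates the baseline, so that a sustained benefit looks like a decline.** That needs a break after audit 36, which conflicts with a pre-intervention model built on 20 points.
- **The correct model doubles the standard error.** Setting about 3.0 against 1.35 compares an effect projected to audit 37 with a jump at audit 21. At the same audit the figures are 3.0 to 3.1 and 2.85.
- **Checking the baseline model on 76 points is circular.** By least squares with a break after audit 20 and separate level and slope terms, later points do not alter the baseline fit.
- **Level and trend are co-primary tests without adjustment.** The article does not declare them so, and naming a single contrast is commonly left to the analysis plan.

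**Conclusion.** The point holds in conditional form. The model as written has no terms for the roll-out, although its 76 points include those 16 audits and the stated primary comparison has a during period.

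For a linear 10-point rise with the break after audit 20, the effect at audit 37 is understated by 10 − 7.3 = 2.7 points, or 10 − 5.5 = 4.5 points with AR(1) weighting at 0.4, and a spurious upward trend change appears. These sizes rest on an assumed effect shape and an inferred break, neither of which the article gives. The bias is zero for an immediate step at audit 21, so it would be wrong to say that the planned analysis is certain to be biased. The written model is safe only if the effect is immediate, and nothing in an eight-week tailored roll-out guarantees that.

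**What to change.** Reconcile the Quantitative analysis section with the three phases in one of two ways:

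- fit a three-segment regression with separate level and slope terms for roll-out (audits 21-36) and post-implementation (audits 37-76); or
- exclude audits 21-36 from the regression, which needs no assumption about how the effect builds up.

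In either case, state where the breaks lie and read the post-implementation effect as the fitted post level minus the projected baseline. Correct the label on the 76 points so that it names all three phases.

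The cost is wording, two extra model terms under the first option, and a standard error at audit 37 of about 3.0 to 3.1 instead of 2.85 points under the assumptions above. No new data are needed. Study status reports that roll-out is under way, so the coding is best fixed before post-implementation data are examined.

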There are several limitations to our study that should be acknowledged. First, the participating hospitals do not routinely collect data on mobilization of patients. Our primary outcome is based on three daily audits of patients being out of bed. Although we validated this measurement against a reference standard, it provides only an estimate of the total mobilization events that patients may undertake. We are not collecting data on evenings and weekends, when families tend to visit, since patients may be mobilized at a different rate during those times. One of the other goals of this project is to work with participating sites to develop a measure for assessing mobility that can be easily incorporated into paper and electronic medical records that are not too onerous for healthcare providers to use; its development will facilitate sustainability of this strategy. Second, the collection of outcome data (specifically, frequency of mobilization) by the research coordinator will not be blinded, and the research coordinator will be aware of the phase of implementation. We are, however, using standardized criteria for this outcome measure. Third, this project highlights the real world challenge of implementing evidence across multiple, different hospitals across a large province. There are always different initiatives underway at hospitals at the same time, all of which compete for hospital resources. We are vulnerable to the risk of initiative fatigue amongst frontline staff. We are using the local working groups to keep track of these other initiatives. Moreover, by allowing the local working groups to contextualize the mobilization intervention to their context, we anticipate alleviating some of this concern. Fourth, because this represents a real world implementation initiative, outcomes are subject to factors such as staff changes, infections outbreaks, and organizational restructuring. We will determine the impact of these confounders through our quantitative analysis as well as the qualitative component of our study.

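### The stated segmented model has no term for first versus second audit of the week, so a systematic difference between the two, if one exists, would mask autocorrelation and moderately inflate type I error

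*Protocol article*

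**What the plan says.** Under Data collection, the Protocol article schedules audits on "two days each week (excluding holidays and weekends"). Table 1 counts 20, 16 and 40 audits for the three phases. Quantitative analysis treats each audit as one point in the series: "time series models will also be estimated for the entire 76 time points (pre- and post-intervention").

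The same section lists the model's terms: "The initial time series regression model included terms estimating changes in the level and trend of outcome rates after intervention", together with a constant and a baseline slope. Nothing in that list refers to the day of the audit. Serial correlation is then tested with Durbin's alternative test and, where needed, corrected by Cochrane-Orcutt. The sample-size statement under Data collection assumes a "correlation for AR(1) of 0.4".

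The article does not say that the two weekdays are the same each week, that the 14 hospitals use the same days, or that mobilization differs between weekdays.

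**The concern.** Each week supplies two consecutive points. If the first audit of the week runs systematically higher or lower than the second, the series zigzags with period two. The four listed terms cannot absorb this, so it goes into the residuals and adds a negative component to their lag-1 correlation. That component offsets the positive correlation the plan expects.

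A lag-1 test then sees little to correct, and a lag-1 correction does too little or, for a large enough difference, works in the wrong direction. The reported standard error of the level change becomes too small, and false positives on the main effect estimate rise.

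**Working it through.** **Inputs.** From the article: 76 points with the intervention starting after point 20; AR(1) 0.4; 66% in bed; 14 hospitals; 35 to 45 patients per hospital per audit; power 0.8; type I error 0.05. Assumed here, because the article does not give them: two-sided testing, the noise SD, and the size *d* of any first-versus-second difference.

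**1. The plan's own figure.** Data collection states 40 points: "In order to detect a 10% decrease for the patients being in bed after the intervention". Take 10 points as absolute, one hospital's binomial SD, a simple before-after comparison of means, and variance inflation (1 + 0.4)/(1 − 0.4) = 2.333. For 40 patients, SD = √(0.66 × 0.34/40) = 0.0749. Points per phase = 2 × (0.0749 × (1.960 + 0.842)/0.10)² × 2.333 ≈ 20.5, so the total is 41.1. With 45 patients the total is 36.5. The stated 40 is therefore reproduced for about 40 to 45 patients, with 0.4 entering as a plain AR(1) inflation and no allowance for audit day.

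**2. Effect on the lag-1 correlation.** Let noise have SD *s* and lag-1 correlation 0.4, with a fixed alternating difference *d* added. The variance becomes s² + d²/4 and the lag-1 covariance 0.4s² − d²/4. The apparent correlation is

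(0.4 − d²/4s²) / (1 + d²/4s²).

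- d = 0.5 SD: (0.4 − 0.0625)/1.0625 = 0.32
- d = 1 SD: (0.4 − 0.25)/1.25 = 0.12
- d = 1.265 SD: 0
- d = 2 SD: (0.4 − 1)/2 = −0.30

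**3. Simulation of the plan's rule.** Settings: 76 points, Gaussian AR(1) 0.4, no true effect, the four stated terms, Durbin's alternative test at 0.05, iterated Cochrane-Orcutt if significant and ordinary least squares otherwise. There were 20,000 runs per setting, so the simulation error is about √(0.10 × 0.90/20,000) = 0.2 points. Results are for the level change.

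| Fixed difference (SD) | Audit term | Autocorrelation flagged | Reported SE / true SD | Type I error |
|---|---|---|---|---|
| 0 | no | 77% | 0.88 | 9.7% |
| 0.5 | no | 50% | 0.83 | 11.6% |
| 0.75 | no | 23% | 0.78 | 13.5% |
| 1.0 | no | 9% | 0.78 | 12.8% |
| 2.0 | no | 90% (negative correlation) | 0.69 | 18.2% |
| 0 | yes | 79% | 0.89 | 9.4% |
| 1.0 | yes | 79% | 0.89 | 9.3% |

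A repeat run gave 9.6% at zero and 13.6% at 1 SD, and about 9% with the term. A three-segment version with breaks after points 20 and 36 (4,000 runs) gave 10.5% at zero and 14.5% at 0.75 SD.

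If the order of the two days varies at random within weeks, masking is weaker. At 0.75 and 1 SD, autocorrelation is flagged in 41% and 20% of runs, and type I error is about 12%.

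**4. What 1 SD means in percentage points, binomial noise only.**

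- Pooled, 14 × 40 = 560 patients, three looks per day correlated by *r*: SD = √(0.66 × 0.34 × (1 + 2r)/3/560). This is 1.5 points at r = 0.3 and 2.0 points at r = 1.
- One hospital, 40 patients, r = 1: 7.5 points, so 0.5 SD is about 3.7 points.

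If hospitals choose their days independently, the pooled contrast averages about 50% of the Monday-to-Friday difference for a linear weekday pattern, and about 24% of the largest weekday difference for an arbitrary pattern. A 2-point pooled contrast would then need a true difference of about 2/0.50 = 4 or 2/0.24 ≈ 8 points.

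**The case against.** The strongest reply is that the harm is conditional on facts the article does not supply. This stands, and it limits the point in several ways.

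- **Alternation.** A reader might infer that the series alternates between two fixed weekdays. The article says only that there are two audit days a week.
- **Weekday differences.** A reader might take the Discussion as conceding that mobilization varies by day, because it notes that some times are not audited "since patients may be mobilized at a different rate during those times". That sentence concerns evenings and weekends. It shows that timing can matter, not that one weekday differs from another.
- **A small gap is enough.** This is fair only for the pooled series under binomial noise. For one hospital the gap needed is not small. Extra-binomial variation, or hospitals auditing on different days, raises it further.
- **Most of the error lies elsewhere.** Type I error is already 9.7% with no difference. A 1 SD difference adds about 3 points (12.8 − 9.7).

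It can also be said that the model is called initial, that the Discussion promises to examine other confounders, and that calendar covariates may be left to a SAP. This has some force. However, the article does enumerate the model's terms, and the only further step it describes is the autocorrelation test and correction, which is the step an omitted audit-day difference would impair.

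**Conclusion.** The point holds as a conditional weakness of the stated model, not as a demonstrated bias. If the two weekly audits differ systematically, the plan's procedure tends to miss the autocorrelation it expects. Type I error for the level change then rises from about 10% to about 12% at 0.5 SD and 13–14% at 1 SD, and the reported standard error falls from about 12% to about 22% too small. With no difference, nothing is lost. With varying weekdays, less is lost.

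The sizes rest on Gaussian AR(1) noise with correlation 0.4 and on an assumed difference for which the article gives no data.

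A reader might infer that an audit-day term would bring the error back to 5%. It would not. The roughly 10% that remains comes from testing and correcting for autocorrelation in a short series, which is a separate issue. The term is worth adding because it costs almost nothing and removes a risk that the present specification leaves open.

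**What to change.** Add a fixed indicator for first or second audit of the week to the segmented model, and fit it before Durbin's test and any Cochrane-Orcutt correction. State whether audit weekdays are fixed and whether hospitals share them.

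The cost is one degree of freedom: 76 − 4 = 72 residual degrees of freedom become 71. In simulation with no difference, the true SD of the level-change estimate moved only from 0.743 to 0.748, and type I error was 9.4% with the term against 9.7% without.

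The indicator absorbs only a systematic first-versus-second contrast. It also worked in simulation when weekdays varied from week to week under a linear weekday pattern. If the order of better and worse days is haphazard, there is no such contrast for it to remove.

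No new data are needed beyond the audit dates. Study status reports baseline collection complete and the intervention being rolled out at all sites, so the term can be specified before the post-implementation data are analysed.
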